**Fig. 3 Fig3:**
[figure not shown]
Examples of lessons within the therapy modules

Abbreviated versions of the coping techniques introduced in the modules are made accessible within the *Toolbox* section of the app; participants are advised to apply these coping techniques when dealing with cravings, stress, negative thoughts, and emotions (e.g. “urge surfing” [57]). In addition, the app features a meditation library with 32 guided meditation audios (see Fig. 4). The meditations, recorded by a professional meditation speaker, are split into 8 categories (relaxation, thoughts and feelings, sleep, body and movement, focus, communication, compassion and gratitude, happiness) and are accompanied by binaural beats [58].

**Fig. 4 Fig4:**
[figure not shown]
App section *Training* consisting of (1) 11 therapy modules, and (2) a *Library* featuring a *Toolbox* and meditation audios

As a means of self-monitoring their cessation behavior, users can track the number of smoked combustible cigarettes in the app. Twelve puffs per cigarette are added to their daily EC puffs and depicted accordingly in the app. Additional nuumi app features include a dashboard that participants can use to track their current pod nicotine concentration, number of daily puffs, as well as progress on the behavioral therapy modules, and meditation minutes. Further, as a self-monitoring tool, users are prompted to answer one question concerning their smoking self-efficacy once per week within the app (“How confident are you that you will be completely abstinent from smoking cigarettes in one year from now?” not confident at all—very confident). Daily check-ins take place throughout the first 14 days of the nuumi program. During these check-ins, participants learn more about EC use and receive tips and motivational content to aid their transition from cigarettes to the EC. Users receive daily push notifications containing motivational and informative text messages based on the therapy modules. No substantial revisions to the app are planned during the trial period, and the anticipated app updates are limited to bug fixes.

The nuumi intervention was developed within the framework of Michaelsen and Esch’s Behavior Change Resource Model (BCRM) [28, 59]. The BCRM states that in the development of effective interventions for health behavior change, it is crucial to identify the resources necessary for successful behavior change and to select behavior change techniques (BCTs) most likely to support individuals in reaching their target behavior. Drawing upon a range of theories from social and health psychology, the behavior change process is commonly characterized as involving distinct stages (non-awareness, awareness, contemplation, planning, initiation, continued action, maintenance) that individuals traverse in pursuit of their goal [60]. At each of these stages, individuals require specific resources, defined as factors of an individual that can affect behavior, which can be categorized into three distinct sets, i.e. external, internal reflective, and internal affective resources which are characterized by both changeable and non-changeable factors [28, 59].

Internal resources are defined as bio-psychological resources pertaining to an individual’s internal state. *Internal reflective* resources are generated, accessed, or improved through effort and conscious deliberation, such as goals and behavioral regulation [28]. *Internal affective* resources, in contrast, can quickly be activated through stimuli without intentional effort, e.g. emotions and their reinforcement [28]. *External* resources refer to the socio-environmental resources that facilitate behavior change and can be provided, modified, or generated by the individual or others [28]. All these resources can be addressed by health BCTs, categorized into three groups: facilitating, boosting, and nudging [28, 59].

*Facilitating* BCTs provide external resources to facilitate new behavior, such as changes in the environment or material resources [28, 59]. The behavior change initiated through facilitating BCTs can, by definition, only last as long as the provision is sustained. However, through the provision of external resources, individuals may acquire a set of skills or routines to sustain the new behavior even when the external support is no longer available [28, 59]. A facilitation-based feature of the nuumi intervention is for example the provision of the EC as a material resource. By gaining access, individuals may acquire skills allowing them to navigate a situation in which they are offered a cigarette; once adopted, the skill can be applied even if the EC is no longer available [28, 59]. *Boosting* BCTs aim to strengthen internal reflective resources [28, 59]. By incorporating cognitive involvement of the individual, boosts foster competencies through changes in skills, knowledge, or decision-making competencies [61]. Boosting-based features included in the nuumi program are e.g. educational videos, audios and interactive exercises within the behavioral therapy part. Theoretically, the strengthening of said resources should generate persistent effects even after the intervention is removed, as competencies including dependence-related knowledge or mindfulness can remain stable over time [28, 59]. Lastly, *nudging* BCTs guide behavior by modifying choice architecture to a specific direction while maintaining freedom of choice [28, 59]. By intentionally applying stimuli, cues, or triggers in an environment, nudging engages affective decision-making elements, rendering the desired behavior more motivationally appealing and intrinsically rewarding [28, 59]. Nudging interventions do not rely on cognitive skills or the provision of external resources to be effective, but rather function through affective components of human motivation and reward processes [28, 59]. These interventions can lead to the formation of new routines without intentional effort from the individual, particularly when they are repeatedly applied [28, 59]. Nudging-based features of nuumi include, among others, the progress tracking dashboard, and daily push notifications containing motivational text messages.

Informed by the BCRM [28, 59], nuumi’s features make use of facilitating, boosting, and nudging techniques to produce behavior change among adults who smoke and are motivated to quit. BCTs were carefully selected and applied, tailoring nuumi to meet their specific needs.

### Data collection, management, and monitoring

Data will be collected via a web-based data collection tool (*LimeSurvey*; LimeSurvey GmbH, Hamburg, Germany). Participants will receive a personalized link to the web-based survey via email and will receive up to two reminder mails within a period of two weeks prompting them to complete the surveys. Data from non-completers will be used to calculate the loss to follow-up rates. Participants will be allowed to skip any question they do not wish to answer. At the end of each web-based survey, the participants can enter feedback or additional comments into a text box.

The university is responsible for storing and protecting the research data. All data will be stored in electronic format on a secure university network location accessible only by authorized members of the research team. The data monitoring committee will comprise the university research team. During data collection, range checks for data values and additional steps to ensure data quality will be conducted by two research team members. Preliminary analyses are planned for t_1_, and t_2_ data after data collection of the respective time point is completed. Primary and secondary outcomes will be assessed with t_3_ and t_4_ data to address the aims of this study. Qualitative data from semi-structured interviews at t_0_ and t_3_ will be analyzed upon completion of all interviews.

App feature utilization data collected by Sanos Group GmbH is stored on a secured network location only accessible by employees of Sanos Group GmbH. Sanos Group GmbH receives the name and email address of the participants for the transmission of the app usage data to the research staff. The participants consent to this data exchange in the informed consent document.

Adverse events will be reported to the Institutional Review Board (IRB) and to the study funder. Documentation of such events will be stored on the university’s secure network location. Participants reporting severe adverse events or side effects from the EC use will be suggested to not use the EC further.

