### Incentives

Participants will receive 10€ for each completed survey (t_1_- t_4_). For participation in the semi-structured interviews, participants can earn another 10€ for each interview for a total incentive of 60€ once the study has ended.

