### Participant timeline

The study will be conducted over a six-month period, during which a total of five surveys will be administered and two interviews will be conducted with a subgroup of participants. Quantitative data collection will take place at t_0_, 4 weeks post-baseline (t_1_), 8 weeks post-baseline (t_2_), 12 weeks post-baseline (t_3_) and 24 weeks post-baseline (t_4_). All participants will receive access to the nuumi intervention directly after t_0_ data collection. Participants will be granted 2 weeks to complete each survey. Primary and secondary outcomes of this study will be answered by analyzing t_3_ and t_4_ data. To minimize fraud potential, survey invitations are personalized and can only be accessed with an individual access key. Surveys can only be completed once by using the individual access key.

Semi-structured interviews will be conducted by research staff with a sub-sample of 15 enrolled participants via videocall or telephone at t_0_ and t_3_. Participants are invited to partake in the baseline survey. Interested participants will indicate their willingness to be invited via email at the end of the baseline survey and will be sent an informed consent form to be signed electronically (Appendix B). The first interview will be conducted within 2 weeks after t_0_, and the second interview within 2 weeks after t_3_. In interview 1, participants will be asked about previous cessation attempts and perceived barriers to smoking cessation, their perceptions, and attitudes towards ECs and towards the use of smartphone apps for smoking cessation. In interview 2, participants will be interviewed about their current smoking and EC use status, their perceptions of the different intervention features, and the perceived effectiveness of the program. Participants may participate in both interviews, however, having participated in the first interview is not a prerequisite for participation in interview 2.

Participant flow and study design are outlined in Fig. 1 in an adapted Consolidated Standards for Reporting Trials (CONSORT-EHEALTH) diagram for pilot and feasibility trials [52, 53].

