#### Primary and secondary outcomes

##### Primary outcome

The primary outcome will be self-reported 7-day point prevalence abstinence from smoking (PPA) at t_3_ and t_4_, operationalized as not having smoked any cigarettes, not even a single puff, in the last 7 days [62].

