### Statistical methods

#### Quantitative data analyses

Analyses will be conducted using the statistical software R, version 4.4.0 (R Core Team, 2024). Given the exploratory nature of this study, data analyses will primarily be descriptive. For categorical variables, frequencies and percentages will be reported. For continuous variables, mean and standard deviation (SD) will be reported. If applicable, statistical comparisons for paired data will be applied to compare scores observed before and after program participation. Statistical significance will be evaluated using a repeated measures two-tailed t-test; the alpha level will be set at 0.05 and a 95% confidence interval will be used. Intention-to-treat (ITT) analyses will be conducted, assuming all individuals not completing a follow-up survey have resumed smoking. In addition, complete cases will be analyzed, i.e. only participants completing the t_3_ and t_4_ survey, respectively, will be included in these analyses. Percentages and patterns of missing data will be assessed using Little’s Missing Completely At Random test and adequate data imputation techniques will be used, if applicable.

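### Non-completers are scored as smoking in the ITT analysis, but the only retrieval contact described is two e-mail reminders to the full survey; a one-question final message would be a cheap improvement

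*Protocol article*

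**What the plan says.** The primary outcome is self-reported 7-day point prevalence abstinence at t3 and t4, "operationalized as not having smoked any cigarettes, not even a single puff, in the last 7 days" (Protocol article, Primary outcome). One answer about the last week settles it.

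That answer is collected in a web survey. Under Participant timeline, "Participants will be granted 2 weeks to complete each survey". Under Data collection, management, and monitoring, participants "will receive up to two reminder mails within a period of two weeks prompting them to complete the surveys". No telephone or text contact and no shortened survey is described. Two features favour a response: "Participants will be allowed to skip any question they do not wish to answer" (same section) and "Participants will receive 10€ for each completed survey" (Incentives).

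Under Quantitative data analyses, the ITT analysis is run "assuming all individuals not completing a follow-up survey have resumed smoking". A second analysis is planned: "In addition, complete cases will be analyzed, i.e. only participants completing the t_3_ and t_4_ survey, respectively, will be included in these analyses". Missing-data patterns will be assessed, and "adequate data imputation techniques will be used, if applicable". No imputation method is named.

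**The concern.** The effort made to obtain the primary answer looks small beside the consequence of not obtaining it. At t3 and t4 the smoking question sits among the PSS-10, SEQ-12 and SF-12 (34 items by their names alone) and further measures of urges, mindfulness, life satisfaction, usability, acceptability, withdrawal, EC dependence and side effects (Secondary outcomes; Other variables; Table 2 in Appendix A). Both reminders point to that same survey. A person who ignores them is scored as smoking in one analysis and left out of the other, although a single reply would settle the matter.

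The study has one arm, so non-response cannot be offset by similar non-response in a comparator. The absolute abstinence rate is the efficacy result. Strengths and limitations intends it as a rough comparison with other cessation interventions, and Objectives makes the study the pilot for an RCT. The Introduction puts long-term abstinence with existing treatments often under 15%, so a shift of a few points could colour that comparison.

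**Working it through.** The plan has no figure of its own to reproduce. The sample size of 70 rests on precedent, and no attrition or abstinence rate is stated.

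**Inputs**
- From the article: N = 70; non-completion = smoking in ITT; complete-case analysis alongside.
- Assumed: non-response share d = 20% to 40%; true abstinence among non-responders q = 10% to 20%; share r of non-responders reached by one further message = 10% to 50%, with those reached assumed representative of all non-responders.

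**Weight of one person.** 1/70 = 1.43 points for each abstainer scored as smoking.

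**Understatement of the ITT rate.** With m = N × d non-responders, of whom m × q are in fact abstinent, the shortfall is m × q / N = d × q.

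| d | q | Shortfall (points) | People out of 70 |
|---|---|---|---|
| 20% | 10% | 2.0 | 1.4 |
| 30% | 15% | 4.5 | 3.15 |
| 40% | 20% | 8.0 | 5.6 |
| any | 0% | 0 | 0 |

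**What one more message recovers.** Recovered amount = r × d × q. In the central case (d = 30%, q = 15%):
- r = 10%: 0.10 × 4.5 = 0.45 points (0.3 of a person)
- r = 20%: 0.20 × 4.5 = 0.9 points (0.6 of a person)
- r = 50%: 0.50 × 4.5 = 2.25 points (1.6 people)

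**The two planned analyses in an illustration.** Assume 21 of 70 do not respond and 24 of the 49 responders are abstinent.
- ITT: 24/70 = 34.3% (Wilson 95% CI 24.2 to 46.0)
- Complete case: 24/49 = 49.0%
- Upper bound if every non-responder were abstinent: 45/70 = 64.3%
- Rate at q = 15%: (24 + 3.15)/70 = 38.8%, which is 4.5 points above ITT

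The planned ITT and complete-case figures lie 14.7 points apart here, and nothing collected under the described procedure shows where between or beyond them the truth lies. Each non-responder whose status is learned narrows that uncertainty, whichever way the answer falls.

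**The case against.** A reader might infer that survey burden is converted directly into treatment failure. The article does not support that. Participants may skip any question, so someone willing to give one answer can open the survey, answer the smoking item and leave the scales. Whether such a survey counts as completed is not stated, so it cannot be assumed that this person would be scored as smoking. Nothing shows that silence after an invitation and two reminders reflects survey length rather than relapse or disengagement. The payment per completed survey is also a real inducement, though not a retrieval contact.

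A reader might also infer that non-responders are smokers throughout the analysis. The rule applies to ITT only: the complete-case analysis omits them and imputation is possible. Scoring missing as smoking is a declared, conservative rule, not a contradiction. That no contact follows the second reminder is inferred from silence, and a fuller procedure may stand in the full protocol, which is not shown.

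Finally, every input to the size is assumed, and recovery of half is optimistic for another e-mail through a channel already ignored. The ITT interval in the illustration is about 22 points wide, and the primary outcome is reported descriptively with no test or threshold attached.

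All of this stands, and it limits the point to a modest one. It does not remove it. Skipping helps only those who open the survey, no described message tells people that one answer would suffice, and neither planned analysis learns the status of those who return nothing.

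**Conclusion.** The point holds as an inexpensive improvement to the procedure described, not as an error. In ITT, non-completion at t3 or t4 means smoking, and the contact described before that rule applies is limited to two reminders to the full survey within two weeks. The resulting shortfall is d × q: 2 to 8 points on the assumed ranges, 4.5 in the central case, and nil if all silent participants are smoking. The realistic gain from one further message is smaller and uncertain, about 0.5 to 2.3 points of the central 4.5.

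The stronger conclusions, that the plan misclassifies people because the survey is long or that the missing = smoking rule is wrong, do not follow from the document. The value of the change lies in replacing part of an assumption with observed answers, in a single-arm pilot whose result is an absolute rate.

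**What to change.** In Data collection, management, and monitoring, add one step at t3 and t4. After the second reminder, send a final message containing only the 7-day abstinence question, reached with the same individual access key and open for a stated short extension beyond the two weeks.

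In Quantitative data analyses, state that:
- this answer is used for the primary outcome in the ITT analysis and flagged as short-form;
- missing = smoking is kept for those who answer neither the survey nor the short form;
- the ITT rate without short-form answers is reported as a sensitivity result.

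The cost is one extra survey item and one automated e-mail at two time points, plus an amendment notified to the IRB, funder, registry and journal as Research ethics approval requires. Short-form answers will come slightly later and in a different format from the rest, which is why they are flagged and the sensitivity result is reported. Recruitment began in October 2023. If t3 and t4 collection is already over, the same step can be carried into the planned RCT.

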### Outcomes

Outcome measures and other variables with their respective assessment time points are shown in Table 2 in Appendix A.

#### Sociodemographic variables

Sociodemographic variables will include age (in years), gender (male; female; diverse), highest level of education (no professional qualification; recognized professional training; bachelor’s degree or equivalent; master’s degree or equivalent; doctorate), employment status (student; employed full-time; employed part-time; employed on a marginal basis (no more than 520€/month); unemployed; retirement pension; disability pension; homemaker; educational retraining; reintegration program; other), household income (in EUR), marital/relationship status (in a partnership living together; in a partnership not living together; single, divorced or separated; widowed), number of children. In addition, participant characteristics will include height (in cm), weight (in kg), pregnancy, previous meditation experience (yes or no), and openness to meditation (yes or no).

#### Primary and secondary outcomes

##### Primary outcome

The primary outcome will be self-reported 7-day point prevalence abstinence from smoking (PPA) at t_3_ and t_4_, operationalized as not having smoked any cigarettes, not even a single puff, in the last 7 days [62].

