### Objectives

The primary objective of this study is to assess initial efficacy of the nuumi program, defined as self-reported 7-day point prevalence abstinence from smoking at 12 weeks and 24 weeks after initiation. Secondary objectives are to examine within-group changes in smoking cessation-related and psychological outcomes, including urges to smoke, perceived stress, mindfulness, self-efficacy to abstain from smoking, subjective health, and life satisfaction. A further secondary objective is to investigate the acceptability of the nuumi program, indexed by perceived usefulness in quitting smoking, user satisfaction, comprehensibility of the content, and usability of the app. The objective of the qualitative interviews is to explore the perspectives of adults who smoke on quitting using electronic cigarettes and apps before the intervention, and their perspective about the intervention after completion. Overall objective of this single-arm trial is to pilot and optimize procedures of a subsequent RCT, in which the nuumi intervention will be compared to a treatment-as-usual (TAU) control group.

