### Participants

Interested individuals are screened for eligibility by completing a brief online questionnaire. Eligible participants are aged 18–65 years, report having smoked at least 5 cigarettes per day (CPD) for at least 12 months, are motivated to stop smoking (Motivation To Stop Scale (MTSS; [51]) > 4 points), have daily access to their own smartphone (iOS 15/Android 11 or more recent), reside in Germany, have access to a personal email account, and report being able to read and write in German.

Ineligibility criteria include self-reported current or planned pregnancy, breastfeeding, a self-reported allergy to vegetable glycerin or propylene glycol, drug and/or alcohol dependence, severe psychiatric or physical illness, a disease or medication associated with a contraindication to the use of EC, and medication that could affect the outcomes of the study (bupropion/ nortriptyline/ varenicline/ cytisine/ clonidine/ antidepressants). Exclusion criteria also include surgery (with anesthesia) in the last 6 weeks, participation in any other smoking cessation program, current use of EC/tobacco heaters/alternative tobacco products/NRT for more than 5 days during the last 30 days, and the inability to consent.

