#### Other variables

##### Smoking behavior-related variables

Smoking behavior-related variables include years of smoking, motivation to quit (Motivation To Stop Scale) [70], number and method(s) of previous quit attempts, use of alternative tobacco products and/or ECs, current participation in other smoking cessation program, current use of NRT, and withdrawal symptoms (Wisconsin Smoking Withdrawal Scale; WSWS2-B) [71]. Additionally, EC dependence is queried (Penn State Electronic Cigarette Dependence Index; PSECDI) [72].

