##### Primary and secondary outcomes

For the primary outcome, 7-day PPA at t_3_ and t_4_, number and percentage of participants self-reporting abstinence will be reported. For the secondary outcomes, measures of frequency and percentages will be reported for 30-days PPA, repeated PPA and continuous PPA, and measures of central tendency will be reported for CPD and urges to smoke. Paired t-tests will be conducted to assess changes in CPD and urges to smoke from t_0_ to t_3_ and from t_0_ to t_4_. Mean and SD will be reported for perceived stress, mindfulness, smoking self-efficacy, subjective health and life satisfaction, and paired t-tests will be conducted to assess within-subject changes in these variables. Acceptability outcomes will be reported descriptively.

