##### Other variables

Frequency measures and percentages will be reported for method(s) of previous quit attempts, use of alternative tobacco products and ECs, participation in other smoking cessation programs, NRT use, and EC dependence. Mean and SD will be calculated for years of smoking, motivation to quit, number of previous quit attempts, and withdrawal symptoms. To assess adherence and engagement, frequencies and percentages of current EC use, and number of days of use will be reported. Mean and SD for engagement with the app will be calculated. Further, frequencies and percentages will be reported for the subjective evaluation of the EC, side effects, and adverse events.

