Informed consent	✓					
Intervention:		✓	✓	✓	✓^a^	
Assessments:						
Participants ‘ characteristics						
Age	✓	✓				
Gender	✓	✓				
Height		✓				
Weight		✓	✓	✓	✓	✓
Pregnancy	✓	✓	✓	✓	✓	✓
Primary outcome						
7-day PPA			✓	✓	✓	✓
Secondary outcomes						
CPD	✓	✓	✓	✓	✓	✓
30-days PPA						
Repeated PPA			✓	✓	✓	✓
Continuous PPA			✓	✓	✓	✓
Urges to smoke		✓	✓	✓	✓	✓
Perceived stress		✓	✓	✓	✓	✓
Mindfulness		✓	✓	✓	✓	✓
Smoking self-efficacy		✓	✓	✓	✓	✓
Subjective health		✓	✓	✓	✓	✓
Life satisfaction		✓	✓	✓	✓	✓
Acceptability		✓	✓	✓	✓	✓
Usability		✓	✓	✓	✓	✓
Adherence			✓	✓	✓	✓
Other variables						
Nicotine dependence		✓	✓	✓	✓	✓
Use of alternative tobacco products	✓	✓	✓	✓	✓	✓
Years of smoking	✓	✓				
Motivation to stop smoking	✓					
Quit attempts and method(s)		✓				
Quit date			✓			
Withdrawal symptoms		✓	✓	✓	✓	✓
EC use	✓	✓	✓	✓	✓	✓
NRT use	✓	✓	✓	✓	✓	✓
Participation in another smoking cessation program	✓	✓	✓	✓	✓	✓
Adverse events			✓	✓	✓	✓
EC dependence			✓	✓	✓	✓
Subjective evaluation and side effects of EC			✓	✓	✓	✓
Dropout			✓	✓	✓	✓
Meditation experience & openness towards meditation		✓				

^a^Participants receive unlimited access to the nuumi app; they can use the nuumi EC as long as they have pods (minimum 12 weeks)

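### The primary outcome is labelled abstinence from smoking but is scored on cigarettes alone, and the alternative-tobacco data collected at weeks 12 and 24 are never linked to that score

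*Protocol article*

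**What the plan says.** The Objectives section sets the target as "self-reported 7-day point prevalence abstinence from smoking at 12 weeks and 24 weeks after initiation". The Primary outcome section keeps that label and gives the rule: "operationalized as not having smoked any cigarettes, not even a single puff, in the last 7 days". The analysis is a count: under Statistical methods, Primary and secondary outcomes, "number and percentage of participants self-reporting abstinence will be reported".

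Other tobacco products are handled as a separate matter in three places:

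- **Entry.** The Participants section excludes "current use of EC/tobacco heaters/alternative tobacco products/NRT for more than 5 days during the last 30 days". Use on up to 5 of the last 30 days is therefore allowed, and the criterion applies at entry only.
- **Collection.** The Smoking behavior-related variables section lists "use of alternative tobacco products and/or ECs". In Appendix A, Table 2, the row "Use of alternative tobacco products" is ticked from enrollment through t4, so it covers both primary time points. EC use has its own row.
- **Analysis.** The Other variables paragraph under Statistical methods says: "Frequency measures and percentages will be reported for method(s) of previous quit attempts, use of alternative tobacco products and ECs".

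**The concern.** The label covers smoking and the rule covers cigarettes. The article does not treat other tobacco products as a kind of cigarette, since it gives them their own exclusion criterion and their own survey variable. Under the written rule, a participant who has stopped cigarettes but smoked some other tobacco product in the last week is abstinent.

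The data that could show this are in the same participant's survey at t3 and t4, but no step brings the two items together. A separate frequency of alternative-product use shows how many people use such products. It does not show how many of them are in the numerator of the primary rate.

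The error has one direction: it can add successes and cannot remove any. The study has a single arm, so no control rate would carry the same error and offset it. The Strengths and limitations section relies on self-report alone and wants the descriptive results to serve as preliminary indicators against other cessation interventions. A reader making that comparison needs to know which products the rate covers.

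**Working it through.** The plan has no figure to reproduce: the Sample size section sets 70 participants without a formal calculation, and no expected abstinence or switching rate is given. The check is therefore a reading of the text, followed by a scale for the effect.

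**Does any rule close the gap?**

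| Rule | Where | Covers a survey completer who smokes another product? |
|---|---|---|
| No cigarettes in 7 days | Primary outcome | No, cigarettes only |
| Exclusion above 5 of 30 days | Participants | No, entry only |
| Non-completers treated as having resumed smoking | Quantitative data analyses | No, non-completers only |
| Frequency of alternative-product use | Other variables (Statistical methods) | No, not linked to abstinence |

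None does.

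**Size per person.** Let *x* be the number scored abstinent on cigarettes and *k* the number of those who smoke another tobacco product. On the intention-to-treat denominator:

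- cigarette-only rate = *x*/70
- rate with other smoked tobacco counted = (*x* − *k*)/70
- difference = *k*/70, which is 1/70 = 1.43 percentage points for each person and zero if *k* = 0

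In the complete-case analysis the denominator is the number of completers. If that is below 70, each person weighs more than 1.43 points.

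**Scale against sampling error.** Both *x* and *k* below are assumptions, because the article gives neither. Intervals are 95% Clopper–Pearson.

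| *x* | *k* | (*x* − *k*)/70 | 95% CI |
|---|---|---|---|
| 21 | 0 | 30.0% | 19.6 to 42.1 |
| 21 | 1 | 20/70 = 28.6% | 18.4 to 40.6 |
| 21 | 3 | 18/70 = 25.7% | 16.0 to 37.6 |
| 21 | 5 | 16/70 = 22.9% | 13.7 to 34.4 |
| 14 | 0 | 20.0% | 11.4 to 31.3 |
| 14 | 3 | 11/70 = 15.7% | 8.1 to 26.4 |
| 28 | 0 | 40.0% | 28.5 to 52.4 |
| 28 | 3 | 25/70 = 35.7% | 24.6 to 48.1 |

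At *x* = 21 the interval is 42.1 − 19.6 = 22.5 points wide. One to five reclassified participants move the estimate by 1.4 to 7.1 points, always downwards. One or two would be hard to see against that width.

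**Can the existing data support a second rate?** Table 2 lists alternative tobacco and EC use as separate rows at t3 and t4, so use of the study EC can be kept apart. The article does not define alternative tobacco products, does not say whether smoked and heated products are separated, and gives no recall window for the follow-up item. The fix has to work without these.

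**The case against.** The strongest reply is that there is no mismatch, because the article uses smoking to mean cigarette smoking. Eligibility is by cigarettes per day, the EC replaces cigarettes, the app tracks combustible cigarettes, continuous abstinence is counted in cigarettes, and the self-efficacy question names cigarettes. The Primary outcome section also states its rule openly and cites a source for it. Most of this stands. It shows that the cigarette-only rate is a legitimate outcome that should be kept, not least for comparison with studies using the same rule. It does not tell a reader of the results that the label excludes other smoked tobacco.

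A second reply is that the data are visible: a large shift to other products would show in the frequency table, and a cross-tabulation could be left to an analysis plan. That is partly right. The information exists, but the only use the article states for it is a separate frequency.

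Third, the number affected is probably small. Regular users of other products are excluded at entry, and the program supplies its own substitute free for at least 3 months. The study is a mainly descriptive pilot with no test or threshold on the primary outcome. All of this stands and limits the weight of the point.

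Three stronger readings are tempting and not supported:

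- A reader might infer that the primary rate is inflated by several points. The article gives no switching rate, so no such figure can be claimed. Six switchers, for instance, would be 6/21 = 29% of the successes if 21 were abstinent, or 6/14 = 43% if 14 were. Nothing in the article suggests that.
- A reader might infer that tobacco-heater users are also wrongly counted as successes. The objective is abstinence from smoking, not from tobacco, so the rule does not fail its objective there.
- A reader might infer that the survey question must be rewritten. Recruitment began in October 2023, and a change during follow-up could make the definition differ between participants or time points.

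**Conclusion.** The point holds as one of labelling and reporting. The outcome is named abstinence from smoking, its rule tests cigarettes only, and the alternative-tobacco data at t3 and t4 are not linked to it. A participant who smokes only another tobacco product is scored a success.

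The effect is 1.4 percentage points per such person out of 70, upwards only. The total is unknown, probably small, and zero if there are no such participants. This rests on reading the rule as written, on the target of 70 as the intention-to-treat denominator, and on the absence from the article of any rule linking the two items. It does not show that the primary rate is materially wrong or that the cigarette-only definition should be dropped.

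**What to change.** 1. Keep the primary rate as defined and label it 7-day abstinence from cigarettes in the objective, the outcome definition and the results.
2. Beside it, at t3 and t4, report a second rate in which participants who report current use of another smoked tobacco product count as non-abstinent, using the item already collected.
3. State that use of the study EC does not count as smoking.
4. Where the existing item does not separate smoked from heated products, or has no 7-day window, count any reported alternative-tobacco use as non-abstinent in the second rate and say so. Do not change the survey during follow-up.

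If the item covers at least the last 7 days and is answered accurately, abstinence from all smoked tobacco lies between the two rates. Participants may skip questions, so give the number of cigarette abstainers who left the item blank.

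The cost is one relabelled outcome and one extra line per time point, with no new data. The second figure may be slightly lower, and it is conservative if the item is not product-specific. Comparability with cigarette-only studies is kept through the first line.
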